### Objectives

The proposed study aims to assess the preliminary effectiveness of an online intervention to promote PA by people with MS (hereafter called an HAPA-MS intervention). We hypothesize that the intervention group will demonstrate (1) higher scores of HAPA components (see the Measures section) and (2) higher frequency, duration, and intensity of PA engagement immediately following the intervention and 6 months or longer after the intervention than the control group.

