### Sample Size Calculation and Power Analysis

According to G*Power 3.1.9.7 [49], when we conducted a power analysis of comparing 2 groups (ie, an intervention group and a control group), an independent *t* test for estimating a sufficient sample size with a 1-tail hypothesis, at a power of 0.80, an alpha level of 0.05, and a medium-large effect size (*d*=0.65-0.70), each group will need to include 26 to 30 participants. The estimated total sample size is 52 to 60 participants. The effect size of 0.65 to 0.70 is based on the large effect sizes (*d*>0.70) of previous internet-based intervention studies [30-35]. When a condition (intervention vs control) is a between-subjects factor and time is a within-subjects factor, a power analysis of a repeated measures within-between interaction (eg, 2 conditions × 3 times) at a power of 0.80, an α level of 0.05, a medium-large effect size (*f*=0.25-0.40), and estimated 8 measures, each group will need to include 8 to 16 participants. The effect size of 0.25 to 0.40 is based on the large effect sizes (ηp^2^>0.14) of previous internet-based intervention studies [30-35]. Therefore, the total sample size of 60 (30 for the intervention group, 30 for the control group) participants is sufficient for the proposed study. In addition, using a wait-list group as a control group is recommended for developmental trials [50].

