### Statistical Analysis

Research assistants will monitor survey completion and accelerometer data sufficiency. When participants return their survey and accelerometers, research assistants will check whether the participants have not responded to the entire survey. If there are missing responses, research assistants will email or call the participants to encourage them to respond to the missing items. The participants will be reminded twice, once each at 2 and 4 weeks, after they return the survey. If their accelerometers do not record valid data, research assistants will contact the participants and ask if they are willing to wear it for 7 days. After those attempts, when we curate the data, we will code missing data as 999.

Our analytic approach will use an intention-to-treat framework, and mixed models will yield unbiased results if the data are “missing at random” [68]. Additional sensitivity analyses will be performed to test for informative dropouts [68]. We will apply pattern-mixture models by stratifying our data by dropout patterns and fitting separate regression models to strata [68]. SPSS 26 (IBM Corp) will be used to conduct descriptive analyses (means, standard deviations), chi-squared tests, independent *t* tests, paired *t* tests, repeated measures ANOVAs, and 2-way (any 2 factors of conditions, disability severity levels, and time) and 3-way (conditions × disability severity levels × time) mixed model ANOVAs. Conditions and disability severity levels are between-subjects factors. Time is a within-subjects factor. We will use 2-way and 3-way ANOVAs to compare measured variables of the intervention and control groups. The significance level is set at .05. We will examine effect sizes of partial ηp2 (0.01, 0.06, and 0.14 as small, moderate, and large effect sizes, respectively) and Cohen *d* (0.20, 0.50, and 0.80 as small, moderate, and large effect sizes, respectively) [69]. We hypothesize that the intervention group will have stronger motivation and self-regulation, more PA, and better health conditions than the control group.

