## Discussion

### Overview

This protocol outlines an RCT to assess the preliminary effectiveness of an online program designed to promote a physically active lifestyle among individuals with MS, utilizing a community-based participatory approach [70]. We expect that the intervention group will be more physically active, especially 6 months after graduating from the program, and will have more phase-specific self-efficacy than the control group. Compared with prior work applying SCT [20,30-35], we used a hybrid framework, HAPA, which provides a comprehensive approach considering an individual’s cognitive processing (ie, different phase-specific self-efficacy), behavior implementation (ie, action and coping planning), and living circumstances (ie, barriers, facilitators, or supportive resources). Peer coaches will lead discussions regarding where and how to gain motivation, what and how to practice self-selected PA and self-set goals each week, and how to cope with barriers and find countable resources to gradually adopt a physically active lifestyle over the program period week by week. We expect that PA logs from the intervention group will show their individualized PA profiles regarding activity types, frequency, and duration.

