Additionally, we will evaluate the program’s capacity to sustain these new lifestyle changes over an extended period, specifically beyond 3 months. To our knowledge, this is one of a few studies implementing a flipped classroom intervention customized to the unique needs and preferences of adults with MS. The adoption of a flipped classroom design, along with peer coaches, not only fosters deep learning experiences but also amplifies interaction and facilitates vicarious learning from the experiences and knowledge of others [71]. This approach empowers participants to take an active role in their learning journey, promoting self-directed and autonomous learning. Additionally, it significantly enhances motivation, thereby cultivating an individual’s interest and capacity for self-regulation. A hybrid theoretical model rooted in evidence-based principles was used to construct the program’s structure and modules. These foundations have been drawn from the research team’s prior research endeavors [36,37,41]. Of equal significance, we have effectively translated these theoretical components into each intervention module, considering the perspectives of individuals living with MS. Using an iterative process to revise each module and collaborating closely with peer coaches helped us ensure that the intervention effectively addresses the specific needs and requirements of the target community. This iterative methodology proved invaluable in our collaboration with community researchers [72]. They provided us with crucial, patient-centered feedback, enabling us to enhance the content of the 8-week modules. It is important to recognize that this process is far from a mechanical repetition; rather, it embodies a deep reflective approach that aids in the development of information tailored to the unique needs of individuals living with MS. Furthermore, our adoption of community-based participatory research not only facilitates the seamless implementation of the program within the community but also enhances its overall applicability. Peer coaches play a vital role in enhancing multiple phases of self-efficacy among members of the intervention group [39,44]. They serve as role models for participants, showcasing a range of successful experiences in sustaining a PA routine while also delivering positive and empathetic feedback to their fellow participants. These actions constitute the primary mechanisms for bolstering an individual’s self-efficacy [39,44]. Moreover, the peer coach’s wealth of experience and expertise in this context is instrumental for fostering connections and personalizing the program further. The practices embedded within the weekly modules will facilitate participants in discovering physical activities that are both feasible and enjoyable, paving the way for the development of a sustainable lifestyle. Research has consistently emphasized the significance of finding enjoyment in sustaining a long-term active lifestyle [73]. Finally, we intend to implement the program using a telerehabilitation method. Considering that a substantial number of people with MS have already used the internet and mobile devices to access health information and resources [24], this online approach holds the promise of being a more effective and valid means to enhance the health and well-being of people with MS.

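### The hypothesis is tied to two visits, but the arms are compared by omnibus ANOVA terms, none of which tests a difference at 6 months

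*Protocol article*

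**What the plan says.** The Objectives section of the protocol article expects higher HAPA scores and more physical activity in the intervention arm "immediately following the intervention and 6 months or longer after the intervention than the control group". The Discussion (Overview) repeats the emphasis on late follow-up: the authors expect that "the intervention group will be more physically active, especially 6 months after graduating from the program", and state that "we will evaluate the program’s capacity to sustain these new lifestyle changes over an extended period, specifically beyond 3 months".

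The Statistical Analysis section lists descriptive statistics, chi-squared tests, independent and paired t tests, repeated measures ANOVAs, and two families of mixed ANOVA. The families are "2-way (any 2 factors of conditions, disability severity levels, and time") and "3-way (conditions × disability severity levels × time) mixed model ANOVAs". One sentence then says how the arms are compared: "We will use 2-way and 3-way ANOVAs to compare measured variables of the intervention and control groups". The significance level is .05. No ANOVA term, contrast or t test is attached to a visit or to either hypothesis.

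The Sample Size section gives two calculations. One is for an independent t test. The other is described as "a power analysis of a repeated measures within-between interaction (eg, 2 conditions × 3 times").

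Data Collection sets assessments at baseline, post-intervention, 3 months and 6 months, with 12 months optional.

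**The concern.** The hypothesis has a direction and names visits. The chosen tests have neither feature. Term by term:

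- **Condition × time** has the null that the arm difference is the same at every visit. A difference at any one follow-up visit can make it reject.
- **Condition main effect** has the null of equal averages over all visits. That average includes baseline, where no effect can exist.
- **Condition × severity × time** has the null that the condition × time pattern is the same at each disability level. This is effect modification, which the Objectives do not hypothesise. A uniform benefit leaves this null true.
- **Severity × time**, which the any-two-factors wording allows, contains no condition term and cannot compare the arms.

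What sets this trial apart is maintenance beyond 3 months. If the deciding test responds in the same way to a benefit that fades and to one that lasts, its result cannot support or refute that claim.

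**Working it through.** **Inputs.** From the article: 25 per arm (Results); four required visits (Data Collection); d = 0.65, the lower end of the range in the Sample Size section; α = 0.05. Assumed: SD 1, compound symmetry, and a within-person correlation ρ of 0.3, 0.5 or 0.7, because the article gives none. Contrasts are two-sided.

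**The article's own figure.** A one-sided independent t test at α = 0.05 and power 0.80 needs 26 per arm at d = 0.70 and 30 per arm at d = 0.65. This reproduces the stated 26 to 30.

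**Condition × time.** Power comes from the noncentral F with

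λ = [n₁n₂/(n₁+n₂)] × Σ(d_t − d̄)² / (1 − ρ), where n₁n₂/(n₁+n₂) = 625/50 = 12.5,

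and df = 3 and 48 × 3 = 144. The sums of squares over baseline, post, 3 months and 6 months are:

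- Post only (0, 0.65, 0, 0): 0.4225 × 3/4 = 0.3169
- Sustained (0, 0.65, 0.65, 0.65): 0.4225 × 3/4 = 0.3169
- Post and 3 months (0, 0.65, 0.65, 0): 0.4225 × 1 = 0.4225
- Fading (0, 0.65, 0.325, 0): 0.2905

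| Pattern | True 6-month effect | λ at ρ 0.3 / 0.5 / 0.7 | Condition × time rejects |
|---|---|---|---|
| Post only | 0 | 5.66 / 7.92 / 13.20 | 48% / 64% / 87% |
| Sustained | 0.65 | 5.66 / 7.92 / 13.20 | 48% / 64% / 87% |
| Post and 3 months | 0 | 7.55 / 10.56 / 17.60 | 61% / 77% / 95% |
| Fading | 0 | 5.19 / 7.26 / 12.10 | 44% / 59% / 83% |

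The first two rows are equal by algebra. An effect d at k of T visits gives d² × k(T − k)/T, which is the same for k = 1 and k = T − 1. Adding a 12-month visit does not break the tie. Under an AR(1) correlation with Greenhouse-Geisser correction (simulation, 2,000 runs, d = 0.65) the two patterns stay close: 47% post only against 46% sustained at ρ = 0.5, and 68% against 62% at ρ = 0.7.

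**The other terms.** For the condition main effect the noncentrality is d̄ × √[12.5 / ((1 + 3ρ)/4)] on 48 df.

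- Post only (d̄ = 0.1625): it rejects in 10–13% of trials.
- Post and 3 months (d̄ = 0.325): 25–37%.
- Sustained (d̄ = 0.4875): 69% / 57% / 48%.

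The three-way term rejects at about 5% when the effect is uniform across severity levels, because its null is then true.

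**A contrast at 6 months.** With baseline as covariate, the noncentrality is 0.65 × √[12.5/(1 − ρ²)] = 2.41 / 2.65 / 3.22 on 47 df, so power for a sustained effect is about 66% / 74% / 88%. Without baseline it is 0.65 × √12.5 = 2.30 on 48 df, so about 61% at every ρ. If the 6-month effect is zero, either contrast rejects at the nominal 5%.

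**The case against.** A reader might infer that the authors will report a significant interaction as proof of maintenance. The article does not say so. It names no deciding term and no rule for claiming a lasting effect. It also lists independent t tests and Cohen's d, which could be applied visit by visit, and simple-effect comparisons after an omnibus test are common practice. Follow-up contrasts may stand in an analysis plan that is not shown, and the trial is presented as a preliminary test. All of this stands, so the misreading is a risk and not something the article plans.

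A reader might also infer that the omnibus tests in general would usually reject for a short-lived effect. That holds only for condition × time, and only at a correlation of about 0.5 or more. At 0.3 the post-only and fading patterns give 48% and 44%. The main effect gives at most 37%, and the three-way term about 5%. The main effect does respond more to a sustained effect than to a post-only one, so the terms read together carry some information. Even so, neither term tests the 6-month difference.

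Nor do the figures support a claim that any targeted contrast gains power. An unadjusted 6-month contrast (61%) is no better than condition × time at ρ = 0.5 (64%) and clearly worse at 0.7 (87%). The gain depends on baseline adjustment.

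The mismatch itself remains. The article does more than leave a detail out: it assigns the arm comparison to the ANOVAs, and one of its two sample-size calculations is for the interaction.

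**Conclusion.** The point holds as a mismatch between the stated hypothesis and the stated between-arm test. No ANOVA term answers the 6-month question, and the t tests that could are attached to no visit or hypothesis. At the article's effect size and achieved enrolment, condition × time rejects equally often for a post-only and a sustained effect (48% / 64% / 87%), and more often still for an effect confined to post and 3 months (61% / 77% / 95%). A significant result would therefore leave maintenance open.

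The exact rates depend on the assumed correlation, compound symmetry, d = 0.65 and complete data. With 22 and 21 completers (25 − 3 and 25 − 4), 12.5 becomes 462/43 = 10.74 and the error df 123. The rates then fall to 42% / 56% / 80% and 54% / 70% / 91%. The equality of the first two patterns is unaffected. The change is worth making, and it calls for no change to the trial's conduct.

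**What to change.** In Statistical Analysis, replace the sentence that assigns the arm comparison to the ANOVAs:

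- Fit one longitudinal model to the follow-up visits, with condition, visit, condition × visit and the baseline value of the outcome (its coefficient free to differ by visit).
- Test hypotheses (1) and (2) by the single-degree-of-freedom between-arm contrasts at post-intervention and at 6 months, the last required visit. Report each as a difference with a 95% CI.
- Claim maintenance only from the 6-month contrast.
- Keep the omnibus condition × time term as descriptive and condition × severity × time as exploratory. Do not count severity × time as an arm comparison.

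Baseline adjustment must be part of the change. For a sustained 0.65 effect it gives the 6-month contrast about 66% / 74% / 88% power, against 48% / 64% / 87% for condition × time. At ρ = 0.7 the benefit is a correctly aimed test, not extra power. Requiring success at both visits would have less power than either contrast alone.

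The cost is wording and a few contrast statements in the software already named, with no new data, visits or participants. The change should be fixed before outcomes are examined by arm. The one loss is that a post-only effect could no longer be presented as support for maintenance.

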#### PA Measures

ActiGraph (wGT3X-BT; ActiGraph LLC) accelerometers will be used to collect PA data during the data collection time points. Participants will be asked to wear the accelerometer around their waist on the nondominant side for 7 days and complete the accelerometer log sheet, including time stamps of wear time. ActiGraph accelerometers were deemed fit for collecting step count data. One study has shown that ActiGraph accelerometers accurately measure steps during moderate and fast walking speeds by both people with MS and control groups. Motl et al [54] indicated a slight underestimation of step count during slow-paced walking using an accelerometer with both people with MS and control groups. Given this, this study will encourage the intervention group participants to keep an optional PA log from the start of the intervention until the end of the study. The log includes recording information on the type, duration, frequency, and intensity of activities performed throughout the day.

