The HAPA battery of risk perception includes the subscales of Disease Threatening, Exam Result Threatening, Risk to Self, Risk to Others, Relative Vulnerability, and Perceived Severity. Each of these subscales has 10 to 13 items based on secondary health conditions in people with MS that are rated on a 7-point scale. Cronbach α values are 0.92 to 0.94 [37]. The HAPA battery of exercise benefits includes the subscales of Exercise Influence on Health Problems (13 items) and Outcome Expectancy (14 items). Cronbach α values are 0.79 to 0.93 [37]. The HAPA battery of motivation includes the subscales of Intention to Do PA (8 items) and Motivational Self-Efficacy (3 items). Cronbach α values are 0.90 and 0.85, respectively [37]. The Cognitive and Behavioral Process of Change Scale has 30 items (15 for the cognitive subscale and 15 for the behavioral subscale) rated on a 5-point scale. Cronbach α values are 0.67 to 0.86 [60]. The Exercise Goal Setting and Planning Scale has 20 items (10 for the goal setting subscale and 10 for the planning subscale) rated on a 5-point scale. Cronbach α values are 0.89 and 0.87, respectively [61]. The Barriers to Health Promotion Activities Scale has 18 items rated on a 4-point scale. Its Cronbach α value is 0.82 [62]. The PA-specific Social Provisions Scale has 24 items rated on a 4-point scale. Its Cronbach α value is 0.89 [57,63]. The Physical Activity Self-Regulation Scale has 12 items rated on a 5-point scale. Cronbach α values are 0.79 to 0.94 [64]. The HAPA battery of PA volition includes the subscales of PA Action Planning (5 items), PA Coping Planning (4 items), Recovery Self-Efficacy (3 items), and Coping Self-Efficacy (13 items) rated on a 4-point scale. Cronbach α values are 0.91 to 0.97 [37].

PA and sedentary behavior will also be assessed using patient-reported scales, that is, the Physical Activity Scale for Individuals with Physical Disabilities (PASIPD) [65] and GLTEQ. Cronbach α values for the PASIPD are 0.37 to 0.65 and for the GLTEQ are 0.46 to 0.94 [65-67].

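### The hypotheses differ between sections, and about 32 scores share one .05 level with no outcome, visit or success rule that decides either hypothesis

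*Protocol article*

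**What the plan says.** **Hypotheses.** The Objectives section predicts "1) higher scores of HAPA components (see the Measures section) and (2) higher frequency, duration, and intensity of PA engagement", both straight after the programme and at 6 months or later. The Abstract gives the same two domains but only a time after the intervention. The Statistical Analysis section expects "stronger motivation and self-regulation, more PA, and better health conditions than the control group", which adds a health domain and gives no time point. The Discussion (Overview) expects more activity, chiefly at 6 months, together with phase-specific self-efficacy.

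**Measures.** The PA Measures and Questionnaire Measures sections list an accelerometer, two activity self-reports, a HAPA battery and many other scales. None is ranked above the others.

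**Analysis.** The Statistical Analysis section lists independent and paired t tests, repeated measures ANOVAs, two-way ANOVAs on any pair of arm, disability level and time, and a three-way ANOVA. It then states: "The significance level is set at .05".

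**Sample size.** The calculation is for a one-tailed comparison of two means with 80% power and α = .05. Its result reads: "a medium-large effect size (*d*=0.65-0.70), each group will need to include 26 to 30 participants". No outcome is attached to that effect size.

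**The concern.** A hypothesis about a family of scales can be judged only if the plan says which scale decides it, when, and how many must differ. Without that, several incompatible results could each be presented as confirmation: a gain in one subscale at the end of the programme, a gain in self-reported activity at 6 months, or better fatigue at any visit. The choice can then follow the data, and the stated .05 does not describe the chance of a false claim.

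The activity hypothesis has the same gap. It can be read from the accelerometer, the PASIPD or the GLTEQ, and the self-reports have modest stated reliability at the low end ("Cronbach α values for the PASIPD are 0.37 to 0.65"; 0.46 to 0.94 for the GLTEQ). The Conclusion says the results could have a substantial effect on lifestyle recommendations, so the claim matters even in a trial described as preliminary.

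**Working it through.** **1. The hypotheses side by side**

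| Section | Domains | Timing |
|---|---|---|
| Abstract | HAPA, activity | after the intervention |
| Objectives | HAPA, activity | immediately, and 6 months or longer |
| Statistical Analysis | motivation and self-regulation, activity, health | none given |
| Discussion, Overview | activity, phase-specific self-efficacy | 6 months stressed for activity |

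**2. Count of scores (PA Measures, Questionnaire Measures)**

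- Labelled HAPA battery: risk perception 6 + exercise benefits 2 + motivation 2 + volition 4 = 14.
- Other psychosocial scales: process of change 2 + goal setting and planning 2 + barriers 1 + social provisions 1 + self-regulation 1 = 7. Running total 21.
- Health: function and disability 2 + pain 2 + fatigue 2 + anxiety and depression 2 = 8 (7 if pain is one score).
- Activity: PASIPD, GLTEQ and at least one accelerometer measure = 3.
- Total: 21 + 8 + 3 = 32 (or 31).

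**3. The plan's own sample size reproduces**

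n per arm = 2(z₀.₉₅ + z₀.₈₀)² / d² = 2(1.645 + 0.842)² / d² ≈ 12.37 / d².

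- d = 0.65: 12.37 / 0.4225 = 29.3, so 30.
- d = 0.70: 12.37 / 0.49 = 25.2, so 26.

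The exact t calculation also gives 30 and 26. The arithmetic is right, but it does not reveal a primary outcome.

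**4. Chance of at least one false-positive HAPA result, one visit**

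Assumptions: no true effect on any scale; K test statistics normal with common correlation ρ (the document gives none); one significant subscale favouring the intervention counts as support. With cut-off c:

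P = 1 − ∫ φ(z) · Φ((c − √ρ·z)/√(1 − ρ))^K dz

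At ρ = 0 this is 1 − Φ(c)^K. For two-sided .05 tests, counting only results that favour the intervention, c = 1.960. For one-sided .05 tests, c = 1.645.

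- K = 14, ρ = 0, two-sided: 1 − 0.975^14 = 0.298.
- K = 14, ρ = 0, one-sided: 1 − 0.95^14 = 0.512.

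| K | ρ | two-sided .05, favourable | one-sided .05 |
|---|---|---|---|
| 14 | 0 | 30% | 51% |
| 14 | 0.3 | 22% | 37% |
| 14 | 0.5 | 17% | 29% |
| 14 | 0.7 | 12% | 21% |
| 21 | 0 | 41% | 66% |
| 21 | 0.3 | 29% | 46% |
| 21 | 0.5 | 22% | 35% |
| 21 | 0.7 | 15% | 24% |

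A single prespecified test would give 2.5% and 5%. Simulation of the same settings agrees to within about one percentage point.

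**5. Two visits**

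If post-intervention and 6 months both count, as the Objectives imply, simulation with an assumed between-visit correlation of 0.6 gives, for the 14 subscales and ρ from 0.7 down to 0, about 20% to 47% (two-sided, favourable) and 32% to 71% (one-sided).

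**6. Power with one deciding outcome**

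The Results section reports 25 per arm. At d = 0.65 to 0.70 and α = .05, power is 73% to 79% one-sided, or about 62% to 68% two-sided. Bonferroni over 14 HAPA scores (.05/14, two-sided) leaves 24% to 29%.

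**The case against.** **The article is condensed.** Primary-outcome labels and multiplicity procedures often sit in a fuller protocol or analysis plan that is not shown. This stands for any complaint that an adjustment method is absent. It does not explain four differing statements of the hypotheses within one published document.

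**The trial is preliminary and will report effect sizes.** True, and a reason not to insist on familywise control over every scale. But the article also plans significance tests of directional hypotheses, so it should say which result answers them.

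**A reader might infer that higher HAPA scores will usually be supported by chance alone.** The document does not support that, for three reasons.
- It contains no rule that one significant subscale is enough; a general pattern could equally be meant.
- For 21 scores at one visit, the chance of a difference in either direction is 66%, 55% or 43% at correlation 0, 0.3 or 0.5. Those figures include differences favouring control; results favouring the intervention occur in 41%, 29% or 22%.
- Separate tests of every score at four follow-ups are an inference. Time is a within-subjects factor in the ANOVAs, and the 12-month visit is optional. Nor is one-sided analysis stated; only the sample size calculation is one-tailed.

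**Not all 21 scores need be HAPA components.** Fair: only 14 carry that label, and the limitations paragraph distinguishes HAPA components from other psychosocial factors. The main figures therefore use 14.

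**Two lesser inferences also fail.** The plan says "this study will encourage the intervention group participants to keep an optional PA log", and a reader might suspect a one-sided data source. But the Discussion uses the log to describe individual profiles, and nothing makes it a between-arm outcome. Likewise "The Barriers to Health Promotion Activities Scale has 18 items rated on a 4-point scale" does not say which end is favourable; that a higher score is worse is an assumption. It shows why direction should be stated per scale, but is not itself an error.

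**Conclusion.** The point holds and should be corrected. The hypotheses disagree in domain and timing across four sections, and about 32 scores share one .05 level with no deciding outcome, visit or success rule. If one significant subscale were accepted as support, the false-positive chance for HAPA at one visit would be about 12% to 30% (two-sided, favouring the intervention, against a nominal 2.5%) or 21% to 51% (one-sided, against 5%) for the 14 labelled subscales. It rises with 21 scores or two visits.

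These ranges rest on assumed correlations of 0.7 to 0, no true effect, and a success rule that the document does not state. They show that the error rate is several times nominal. They do not show that a chance finding is more likely than not: above 50% is reached only under some settings, such as independent one-sided tests or several visits.

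**What to change.** Before outcome data are analysed, and with the date recorded:

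1. State one set of hypotheses and use it in the Abstract, Objectives, Statistical Analysis and Discussion, including whether health outcomes belong to it.
2. Name one outcome and one visit that decide the efficacy claim, tested at .05 with sidedness stated. One example is accelerometer moderate-to-vigorous minutes per day at 6 months, the visit the Discussion stresses and the last that is not optional. The investigators may prefer another; what matters is that one is named.
3. For hypothesis 1, list the scales that count, the favourable direction of each, and the visit.
4. Report the remaining scores, visits, health outcomes and three-way terms as estimates with 95% confidence intervals, labelled exploratory. If a confirmatory HAPA claim is wanted, state a multiplicity adjustment and accept its price, such as the 24% to 29% power under Bonferroni over 14 scores shown above.

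This changes wording only and needs no new data. The downside is that fewer results can be called significant.

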**Objective:**

This study aims to test the preliminary efficacy of a codeveloped, online self-management intervention based on the health action process approach (HAPA) adapted for people with MS to cultivate a physically active lifestyle.

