## Results

The study was funded in April 2018. We conducted peer coach selection interviews from July 2018 through October 2018. Peer coaches codeveloped and evaluated each module of the online program from November 2018 through January 2020. We iteratively revised the modules based on the peer coaches’ feedback. During the pandemic, participants preferred to discontinue the study. The modules also had to be migrated from the Moodle system to a new online learning system, Canvas, in 2022 due to changes in the university’s online learning system.

We invited peer coaches to review the accessibility of online modules in fall 2022. We finalized the module accessibility and trained peer coaches on how to use the online modules in December 2022. Since February 2023, we have recruited 50 participants to the trial who have been assigned to the intervention group (n=25) or control group (n=25). During the follow-up stage, 3 participants dropped out of the intervention group, and 4 participants dropped out of the control group. Enrollment ended in 2024, and data collection is expected to conclude by December 2025, with results anticipated to be published in January 2026.

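### The planned effect-size measure, sample partial eta squared, is biased upward: at 43 to 50 participants its average under no effect is already about twice the 'small' benchmark

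*Protocol article*

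**What the plan says.** The Statistical Analysis section of the protocol article plans two-way and three-way mixed ANOVAs with condition, disability severity and time as factors. It then names the effect-size measures and their benchmarks: "We will examine effect sizes of partial ηp2 (0.01, 0.06, and 0.14 as small, moderate, and large effect sizes, respectively", and for Cohen d "0.20, 0.50, and 0.80 as small, moderate, and large effect sizes, respectively". Just before this it states: "The significance level is set at .05". It names no bias-adjusted measure and no interval for the effect sizes. It does not give the number of disability severity levels.

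The aim in the abstract is to "test the preliminary efficacy of a codeveloped, online self-management intervention". The Results section reports 50 participants assigned, 25 per arm, and that "3 participants dropped out of the intervention group, and 4 participants dropped out of the control group". The Data Collection section gives four assessment times plus an optional fifth at 12 months.

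**The concern.** Partial eta squared is a ratio of sums of squares, so noise alone makes it positive. The smaller the trial and the more numerator degrees of freedom a term has, the larger its value under no effect. Benchmarks of 0.01, 0.06 and 0.14 are useful only if a value above 0.01 is some evidence of more than noise. If the null average already exceeds 0.01, the lowest category does not separate signal from noise. Because the null average depends on the degrees of freedom, the same label can also mean different things in the two-way and three-way models.

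This matters for a preliminary trial because readers of its report are likely to look at effect sizes as well as p values. The protocol's own sample size used effect sizes from earlier studies: "The effect size of 0.65 to 0.70 is based on the large effect sizes".

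**Working it through.** **Inputs.** Benchmarks 0.01, 0.06 and 0.14 (Statistical Analysis). N = 50 assigned; 50 − 3 − 4 = 43 after dropout, 22 and 21 per arm (Results). Four visits, without the optional one (Data Collection). The number of severity levels is not stated, so 2, 3 and 4 are assumed in turn.

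**The plan's own figure.** A one-sided t test at 0.05 with power 0.80 needs 30 per group for d = 0.65 and 26 for d = 0.70. This agrees with the protocol ("each group will need to include 26 to 30 participants"), so the point does not touch that calculation.

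**Formulas.** Under no effect, partial eta squared follows a Beta(df1/2, df2/2) distribution with mean df1/(df1 + df2). The chance that it reaches a cut-off c is P(F ≥ [c/(1 − c)] × df2/df1). For N participants, k visits and g severity levels, the degrees of freedom are:

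- condition: 1 and N − 2
- condition by time: k − 1 and (k − 1)(N − 2)
- condition by severity by time: (g − 1)(k − 1) and (k − 1)(N − 2g)

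**Null means.**

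- Condition: 1/49 = 0.020 (N = 50) and 1/42 = 0.024 (N = 43).
- Condition by time, four visits: 3/147 = 0.020 and 3/126 = 0.024.
- Three-way, 3 levels assumed: 6/138 = 0.043 and 6/117 = 0.051.
- Three-way, 2 levels: 3/141 = 0.021 and 3/120 = 0.025.
- Three-way, 4 levels: 9/135 = 0.067 and 9/114 = 0.079.

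**Chance of reaching each benchmark when the true effect is zero (N = 50 / N = 43).**

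| Term | 0.01 or more | 0.06 or more | Smallest value significant at .05 |
|---|---|---|---|
| Condition | 49% / 52% | 9% / 11% | 0.078 / 0.090 |
| Condition by time, 4 visits | 69% / 74% | 3% / 5% | 0.053 / 0.061 |
| Three-way, 2 levels (assumed) | 71% / 76% | 4% / 6% | 0.055 / 0.064 |
| Three-way, 3 levels (assumed) | 97% / 98% | 22% / 32% | 0.090 / 0.105 |

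For condition and condition by time, 0.14 is reached in at most about 1% of null cases. A simulation with four visits and autoregressive correlation of 0.7 gave nearly the same means: 0.021 and 0.024 for condition by time, 0.044 and 0.052 for the three-way term with 3 levels.

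**A bias-adjusted measure.** Partial epsilon squared is df1(F − 1)/(df1 × F + df2). Its null average is zero. It reaches 0.01 under no effect in 23% / 24% of condition tests and 22% / 24% of condition by time tests. So the adjustment removes the bias but not the noise, and an interval is still needed.

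**Cohen d.** Under no effect its standard error is √(1/25 + 1/25) = 0.283, or √(1/22 + 1/21) = 0.305. The 95% half-width is 1.96 times this, 0.55 to 0.60. An absolute value of 0.20 or more occurs in 48% / 52% of null cases, and in the hypothesised direction in 24% / 26%.

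**The case against.** The strongest reply is that the protocol only says effect sizes will be examined. The benchmarks are conventional and stand next to a .05 significance level. A reader might infer that null results will be reported as small or moderate effects. The text does not support that: it nowhere says that a label will be attached to a non-significant term or will replace the test. If labels are kept to significant terms, the test screens out most of the noise. For condition by time at N = 50, a value of 0.06 is already significant, so the *moderate* benchmark adds almost no false signals there. This stands, and it limits the point to what the text leaves open.

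Three further limits also stand. First, for the condition effect, reaching *small* under the null is about a coin flip, not the usual outcome. Second, the null mean of 0.05 and the 22 to 32% for *moderate* need a three-level severity factor, which the protocol does not state; those terms also concern effect modification, not the main hypotheses. Third, it is tempting to say that d has the same fault. It does not: d is signed and averages zero under no effect, so its problem is imprecision only.

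It can also be said that confidence intervals are a detail an article leaves to the full analysis plan. That is fair for their absence. But the choice of partial eta squared and its benchmarks is stated here, and it is that choice which is biased at this sample size.

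**Conclusion.** The point holds as a weakness in the stated choice of measure, not as an error in a stated figure. For the two terms that carry the arm comparison, the null average is 2.0 to 2.4 times the *small* benchmark, so passing 0.01 says almost nothing about an effect. Values from 0.01 up to roughly 0.05 to 0.09 are non-significant, yet the protocol does not rule out calling them small or, for the condition effect, moderate. Crossed terms are worse with three or more severity levels and little different with two.

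The figures assume 43 to 50 analysed participants, four visits and classical ANOVA degrees of freedom. This is a low-cost improvement; it does not undermine the trial's design or its tests.

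**What to change.** In the Statistical Analysis section:

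1. Replace partial eta squared with partial epsilon squared, by the formula above, or partial omega squared. For terms with several degrees of freedom, add a 90% interval; its lower limit exceeds zero exactly when the F test is significant at .05.
2. For each between-arm comparison, report the mean difference in its own units and d, each with a 95% confidence interval.
3. State that no size label will be attached to an effect whose interval includes zero.
4. State the number of disability severity levels, since the null value of the crossed terms depends on it.

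The cost is a few lines of text. The adjusted measures follow from F values and degrees of freedom that the ANOVA output already gives, and no new data are needed. The downside is that fewer effects will carry a label and the reported sizes will be somewhat smaller. A stricter rule, labelling only when the whole interval clears a benchmark, is not recommended: with half-widths of 0.55 to 0.60 for d, an observed d of 0.70 would have a lower limit of only about 0.10 to 0.15, so even effects of the planned size would mostly go unlabelled.
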